### Training of LHWs

The LHW programme of Pakistan consists of a community-based group of first-level health workers with the principal mandate of home-based maternal and child health. The recruitment process is well defined and selection criteria include: at least 8 years of education with middle school pass, local residency, recommendation from the community and preferably married.^32^ Once selected, they receive 15 months of basic training in mid-wifery and family planning using standardised training manuals and curriculum, and periodic refresher training courses. Each of these LHWs is typically responsible for approximately 1000 people, or 150 homes, and often serve as the primary healthcare contact in these rural communities.^32 33^

We chose LHWs as study personnel due to their access to homes on regular monthly basis. We trained intervention and control LHWs in separate groups for all of the following: (1) classification of ARI (no pneumonia, pneumonia, severe pneumonia) using standard acute respiratory infections training modules (WHO and IMNCI), (2) identification of danger signs and (3) case management of pneumonia at home with oral amoxicillin and severe pneumonia with stat dose of antibiotic before hospital referral. Intervention LHWs received an additional training in using a pulse oximeter and obtaining a valid reading. The principal investigator (PI) led these training sessions with senior trainers of the LHW programme (lady health supervisors).

### Participant recruitment and study procedures

#### Intervention delivery

Children aged 0–59 months with cough and/or difficult breathing during regular home visits of LHWs will be assessed for first, signs and symptoms of severe pneumonia (fast breathing/chest in-drawing and one or more danger sign (unable to eat/drink, vomiting, convulsion and lethargy/unconsciousness) and/or stridor)) and second, hypoxaemia (SpO2 <92%) using a handheld pulse oximeter (Masimo Rad-5v) to measure blood oxygen saturation level. LHWs will also do case management of children with pneumonia and severe pneumonia. A 3-day course of oral amoxicillin will be given to children with pneumonia at home, whereas children meeting referral criteria (severe pneumonia alone, hypoxaemia alone or severe pneumonia and hypoxaemia) after obtaining informed consent (online supplemental appendix 2), will be administered a stat dose of oral amoxicillin and referred to nearest referral hospital (DHQ Kotri).

The study investigators will have provided these pulse oximeters to the LHW programme in advance and highlighted which ones will receive them. Physicians at the referral centre serving the intervention clusters will also receive handheld pulse oximeters. All the LHWs and staff will be trained on the use, and maintenance of these pulse oximeters. Children with severe pneumonia with or without hypoxaemia will be advised to go to hospital for antibiotics and oxygen, using the PO reading as a tool to convince parents. Children with hypoxaemia alone, without signs of severe pneumonia, will be referred to hospital to rule out cyanotic congenital heart disease. Name of the predesignated health facility with available oxygen and study physician will be provided to all the LHWs so that Study Workers (non-LHW study personnel) can coordinate with study physicians and ensure the patient has reached and is receiving safe and recommended care at referral facility. Project staff will pretest and regularly monitor PO accuracy and quality of readings.

Hypoxaemia will be defined as an SpO2 <92%. SpO2 measurement will be recorded after 1 min of stable observation. If the SpO2 comes 92% or less, the child will first be assessed for nasal obstruction with readings repeated after applying nasal saline drops. If repeat reading shows hypoxaemia, the child will be referred to nearest designated referral hospital and admitted for oxygen via nasal or nasopharyngeal route and intravenous antibiotics, as per recommendations.

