### Participant

Any child aged 0–59 months having signs and symptoms of acute respiratory illness (cough, fever, difficulty in breathing) in intervention clusters will undergo assessment of (1) signs and symptoms of severe pneumonia and (2) pulse oximetry during monthly LHW home visits. Presence of severe pneumonia with or without hypoxaemia, or hypoxaemia alone will merit hospital referral (non-facilitated). Any child aged 0–59 months having signs and symptoms of acute respiratory illness (cough, fever, difficulty in breathing) in control clusters will undergo assessment of (1) signs and symptoms of severe pneumonia alone. Presence of severe pneumonia will merit hospital referral (non-facilitated). Exclusion criteria will include lack of consent and, non-availability (lost to follow-up, migration) on days of scheduled follow-up visits (days 7 and 14). Those who accepted referral but did not show up at hospital will be included in final analysis.

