#### Implementation of active control: clinical signs assessment

Children aged 0–59 months with cough and/or difficult breathing during regular home visit will be assessed by LHWs for signs and symptoms of severe pneumonia (fast breathing/chest in-drawing and one or more danger sign (unable to eat/drink, vomiting, convulsion and lethargy/unconsciousness) and/or stridor)). A 3-day course of oral amoxicillin will be given to children with pneumonia at home, whereas children with severe pneumonia (eligible for recruitment) will be requested for informed consent and offered stat dose of oral amoxicillin and referral to nearest referral hospital.

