### Data management

Screening data will be collected on paper by LHWs. CRF and HPF will be collected on electronic forms. To ensure proper implementation of the intervention, the field supervisors will make spot checks and will arrange monthly refresher group sessions of the first-line health workers in which the problems encountered will be discussed and resolved. In addition, the data collection activity will be carried out by teams consisting of LHWs/CHWs and study staff will be further monitored by field supervisors who will perform a check on a subset (5%) of households.

An information system will be set up to keep track all patients screened and enrolled and a filing system to keep all study related records—case history records, study protocol or related documentation and drug distribution records. The coordinator at the site will be responsible for the completeness and accuracy of all the study materials.

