### Data analysis

The primary analysis for each outcome will perform on an ‘intention-to-treat’ basis, that is, all children included in the analysis who were enrolled in the study according to the group to which they were allocated. All analyses will account for the cluster randomised design to ensure correct type I error rates and CIs.^35^ Baseline characteristics will be compared by analysing differences in means and proportions among the study arms. Categorical outcomes will be compared using χ^2^ test and continuous outcomes using Student’s t-test. For analysis of predictors of referral acceptance, generalised linear model will be used with logit link function. The univariate analysis will be conducted to explore the independent effect of each predictor on outcome. The variables significant at a liberal p<0.20 will be included in multivariate model for adjustment. The results will be reported as relative risk with 95% CI. Type 1 error will be set at 5% level. All analysis will be done using STATA V.15.

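### Consent is sought after the oximeter reading in one arm and after clinical signs only in the other, and decliners are excluded, so differential consent could bias the acceptance ratio in either direction

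*Protocol article*

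**What the plan says.** Intervention delivery describes an assessment in two steps: clinical signs first, and "second, hypoxaemia (SpO2 <92%) using a handheld pulse oximeter (Masimo Rad-5v) to measure blood oxygen saturation level". Children who then meet referral criteria are, "after obtaining informed consent (online supplemental appendix 2), will be administered a stat dose of oral amoxicillin and referred". So the reading comes before the consent request.

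The control section has no reading: "children with severe pneumonia (eligible for recruitment) will be requested for informed consent and offered stat dose of oral amoxicillin and referral".

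Participant sets the entry filter: "Exclusion criteria will include lack of consent". Data analysis defines the intention-to-treat set as "all children included in the analysis who were enrolled in the study according to the group to which they were allocated". A child whose family declines consent is therefore in neither numerator nor denominator.

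Three other statements bear on this. The Abstract has LHWs doing the recruiting in both arms. Strengths and limitations states that the trial cannot be blinded. Randomisation and masking shows that whole LHW catchments were allocated, so the arm is fixed before any child is found.

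**The concern.** The outcome is whether a family acts on the LHW's advice to go to hospital. Agreeing to join the study, when the same LHW asks, may draw on a similar willingness. If it does, the consent step removes some families who would have refused referral, and it does so after randomisation, when the arms differ in what has already happened in the home.

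If families are readier to consent once a reading has been taken, reluctant families stay in the intervention denominator but drop out of the control denominator, and a real effect is partly hidden. If they are less ready, or the LHW presses less, an effect could appear where there is none. The article's claim that the design prevents allocation bias concerns assignment of clusters and does not reach this later step.

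The article also leaves open whether a family that declines the study is still referred. Participant treats the clinical finding as sufficient for referral. The first paragraph of Intervention delivery places referral after consent. That section's closing paragraph refers on a repeat low reading without mentioning consent. The control section pairs the consent request with the referral offer. A family that is never referred cannot accept.

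**Working it through.** **Inputs.** From Sample size: true acceptance 10% (control) and 15% (intervention), so the design ratio is 15/10 = 1.50; ICC 0.001736; total 4160. From Randomisation and masking: 188 LHWs, taken as 94 per arm. From Data analysis: 5% type I error, taken as two-sided. Decline rates are not given, so all those below are assumptions.

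**Formula.** Let p be true acceptance among all eligible children, d the proportion declining consent, and q the acceptance that decliners would have shown. Among enrolled children, observed acceptance = (p − d·q)/(1 − d). If q = p, the observed rate is p and there is no bias. If all decliners would refuse referral (q = 0), it is p/(1 − d).

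**Extreme case, q = 0, true ratio 1.50**

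| Declining, control/intervention | Observed control | Observed intervention | Ratio | Relative increase lost |
|---|---|---|---|---|
| 10%/5% | 0.10/0.90 = 11.1% | 0.15/0.95 = 15.8% | 1.42 | 16% |
| 20%/10% | 0.10/0.80 = 12.5% | 0.15/0.90 = 16.7% | 1.33 | 33% |
| 20%/5% | 12.5% | 15.8% | 1.26 | 47% |
| 30%/10% | 0.10/0.70 = 14.3% | 16.7% | 1.17 | 67% |

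The last column is (1.50 − ratio)/0.50.

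**Milder case, q = p/2.** Observed acceptance = p(1 − d/2)/(1 − d). For 10%/5%: control 0.10 × 0.95/0.90 = 10.6%, intervention 0.15 × 0.975/0.95 = 15.4%, ratio 1.46, loss 8%. For 30%/10%: control 0.10 × 0.85/0.70 = 12.1%, intervention 0.15 × 0.95/0.90 = 15.8%, ratio 1.30, loss 39%.

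**Equal declining.** With q = 0 and the same d in both arms, (1 − d) cancels and the ratio stays at 1.50. If instead the share of would-be refusers who consent is equal in both arms, at 0.7 to 0.9, the ratio is 1.47 to 1.49.

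**Reverse direction, no true effect (10% in both arms), q = 0.** With control declining of 9%, observed control acceptance is 0.10/0.91 = 11.0%.
- Intervention declining 18%: 0.10/0.82 = 12.2%, ratio 1.11.
- Intervention declining 27%: 0.10/0.73 = 13.7%, ratio 1.25.
- Intervention declining 36%: 0.10/0.64 = 15.6%, ratio 1.42.

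With 2080 children per arm, cluster size 2080/94 = 22.1 and design effect 1 + (22.1 − 1) × 0.001736 = 1.037, the chance of a falsely significant benefit is about 22%, 74% and 99%. The total of 4160 is taken as stated here; how it was derived is a separate matter and does not affect the ratios.

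**The case against.** The strongest reply is that nothing in the article shows that decliners are less compliant. The trial keeps consent and referral apart: consenting families who refuse referral are visited and recorded, and those who accept but never arrive are analysed. With planned acceptance of 10% to 15%, some 85% to 90% of enrolled families are expected not to accept, so consent looks like a weak filter on willingness. This stands against a stronger reading that a reader might infer, namely that both arms are known to be enriched for compliant families. That is an inference without data, and enrichment of equal size would hardly matter. It does not exclude a difference between arms.

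A reader might also infer that the reading is used to win consent. The article does not say so: "using the PO reading as a tool to convince parents" belongs to the sentence on advice to go to hospital. Nor does it say that parents are told the reading before they are asked. The consent wording is in an appendix not shown. What stands is that the reading has been taken by then, in one arm only, by a recruiter who knows the arm.

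Nor do the enrolment counts in Study status (235 cases, 184 controls) show differential consent. If these are the two arms, the wider eligibility in intervention clusters, differences in detection, or chance could explain the gap.

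Finally, reporting refusals and adding sensitivity analyses often belong in an analysis plan, and the article promises that "An information system will be set up to keep track all patients screened and enrolled". Their absence is not the fault. The order of consent and the exclusion of decliners are fixed here.

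**Conclusion.** The concern holds as a risk created by the plan as written: an enrolled-only analysis after a consent step that is placed differently in the two arms, run by unblinded recruiters after allocation. The bias could go either way, and neither its direction nor its size can be known from the article. The illustrative loss of 16% to 67% of the relative increase assumes that every decliner would refuse referral and that declining differs between arms by 5 to 20 percentage points. It shrinks to 8% to 39% if decliners would accept at half the overall rate, and to nothing if they resemble consenters.

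It also should not be read as a finding that the plan withholds referral from decliners. The passages differ and need reconciling; they do not settle the question. The point deserves action because the cost is modest and, at the reported count, 235 + 184 = 419 of 4160 children (about 10%) had been enrolled.

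**What to change.** 1. For children meeting the clinical severe-pneumonia criteria, ask consent at the same point and with the same wording in both arms: after the clinical-signs step and before the oximeter reading is taken or disclosed. The existing order of assessment allows this without seeking consent for every child with respiratory illness. Children with hypoxaemia alone can be identified only in the intervention arm. They would be asked after the reading and kept out of this comparison.
2. Pre-specify a sensitivity analysis by cluster and arm that includes children already enrolled. The numerator is children meeting the clinical criteria who reach hospital; the denominator is all screened children meeting the same criteria, from de-identified screening counts. Consent decliners count as non-acceptors, stated as a bounding assumption. In the 20%/5% case this returns 12.5% × 0.80 = 10% and 15.8% × 0.95 = 15%, ratio 1.50, because that case assumes the same thing.
3. Report consent refusals by arm.
4. Reconcile Participant, both relevant paragraphs of Intervention delivery, and the control section on whether referral depends on study consent.

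The costs are ethics committee agreement to use anonymous counts, retraining at the existing monthly refresher sessions, and a change of consent order partway through enrolment, so results before and after the change should also be reported. The change reduces the risk but does not remove it, because LHWs still know their arm.

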#### Implementation of active control: clinical signs assessment

Children aged 0–59 months with cough and/or difficult breathing during regular home visit will be assessed by LHWs for signs and symptoms of severe pneumonia (fast breathing/chest in-drawing and one or more danger sign (unable to eat/drink, vomiting, convulsion and lethargy/unconsciousness) and/or stridor)). A 3-day course of oral amoxicillin will be given to children with pneumonia at home, whereas children with severe pneumonia (eligible for recruitment) will be requested for informed consent and offered stat dose of oral amoxicillin and referral to nearest referral hospital.

#### Procedure at referral facility

Children who accept hospital referral in both intervention and control clusters and reach hospital premises with LHW referral slip will be assessed by study physician at the referral centre. An SMS notification with brief details of referred child will have been provided to trained study personnel (study physician) in advance at time of referral at both the referral facilities. Children with severe pneumonia and/or hypoxaemia as per LHWs who reach referral hospital premises will be examined and subjected to pulse oximetry again by the study physician at referral facility. If signs and symptoms of severe pneumonia are present, the child will be admitted for further appropriate treatment (oxygen therapy via nasal or nasopharyngeal route and intravenous antibiotics, etc) and if the symptoms are not severe (absence of danger sign), the child will be treated in outpatient care as per the standard of referral facility. All the children admitted at referral facility will undergo 12 hourly monitoring by study personnel and filling of CRF and hospital physician form (HPF) at days 1, 7 and 14. Those children who refused the referral will be visited by study community health workers after 24 hours to confirm referral refusal and to fill CRF.

Preliminary meetings will be held with the executive director health Jamshoro, director general health Sindh, in-charge LHW programme Sindh and in-charge paediatric units LUMHS to ensure their cooperation through study duration. Emergency and paediatric unit staff at the referral facilities along with study personnel (physician/nurse) will be trained on management of severe pneumonia according to the integrated management of neonatal and childhood illnesses (IMNCI) guidelines.^34^ A baseline survey will be conducted at the health facilities to ensure availability of oxygen and necessary intravenous antibiotics. Even though it is ideal to guarantee sustainable oxygen systems at the two chosen referral public sector hospitals, this study does not provide oxygen, and therefore, aims to assess ‘real-life’ situations in public hospitals and their impact on severe pneumonia outcomes with or without hypoxaemia. LHWs will be incentivised on basis of their contribution to the study activities.

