**Methods and analysis:**

A cluster randomised controlled trial using pulse oximetry as intervention for children with severe pneumonia will be conducted in community settings. Children aged 0–59 months with signs of severe pneumonia will be recruited by LHWs during routine visits in both intervention and control arms after consent. Severe pneumonia will be defined as fast breathing and/or chest in-drawing, and, one or more danger sign and/or hypoxaemia (Sa02 <92%) in PO (intervention) group and fast breathing and/or chest in-drawing and one or more danger sign in clinical signs (control) group. Recruits in both groups will receive a stat dose of oral amoxicillin and referral to designated tertiary health facility. Analysis of variance will be used to compare baseline referral acceptance in both groups with that at end of study.

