**Figure 1 F1:**
[figure not shown]
Trial profile. LHW, Lady Health Worker, PO, Pulse Oximetry.

The primary outcome is hospital referral acceptance in children under 5 with severe pneumonia and to identify demographic and clinical predictors of hospital referral acceptance. The predictors will include distance of child home to referral facility, socioeconomic status of household, parental education, child age, nutritional status, respiratory rate, temperature, hypoxaemia and presence of other illnesses.

Secondary outcomes include duration of oxygen therapy, treatment failure, duration of hospital stay, vital and health status of child at day 7th and 14th.

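### A child still below 92% SpO2 at hospital but without a danger sign is admitted under one rule and sent to outpatient care under another

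*Protocol article*

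**What the plan says.** **Intervention delivery.** The threshold is fixed: "Hypoxaemia will be defined as an SpO2 <92"%. A low first reading is repeated after nasal saline drops. If the repeat is also low, "the child will be referred to nearest designated referral hospital and admitted for oxygen via nasal or nasopharyngeal route and intravenous antibiotics". No danger sign is required.

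**Procedure at referral facility.** Referred children who arrive "will be examined and subjected to pulse oximetry again by the study physician at referral facility". Two disposition clauses follow. The first admits the child when signs of severe pneumonia are present. The second reads "if the symptoms are not severe (absence of danger sign), the child will be treated in outpatient care". SpO2 appears in neither clause.

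**Definitions of severe pneumonia.** There are two. The Abstract (Methods and analysis) requires fast breathing or chest in-drawing together with "one or more danger sign and/or hypoxaemia (Sa02 <92%) in PO (intervention) group", so in that arm hypoxaemia can stand in for a danger sign. Intervention delivery instead assesses clinical signs first (fast breathing or in-drawing with a danger sign and/or stridor) and hypoxaemia second, as a separate item.

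**Hypoxaemia alone.** This is a referral criterion in intervention clusters (Study aims and design; Participant; Intervention delivery). Its stated purpose is diagnostic: "Children with hypoxaemia alone, without signs of severe pneumonia, will be referred to hospital to rule out cyanotic congenital heart disease". No admission rule is attached to that sentence.

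**The concern.** The two sections appear to give opposite instructions for the child the intervention is meant to find: one whose low saturation would be missed on danger signs alone. If hospital staff follow the referral-facility section literally, a child still below 92% goes to outpatient care, although the family was sent on the strength of the reading and the other section requires admission for oxygen. The Introduction itself cites a 4.3-fold mortality risk for pneumonia with hypoxaemia, there defined as below 90%.

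There is a smaller statistical consequence. The article states: "Secondary outcomes include duration of oxygen therapy, treatment failure, duration of hospital stay". Each of these depends on whether a child is admitted, so if physicians resolve the conflict differently, the outcomes partly reflect which sentence was followed. The primary outcome is settled before the rule operates.

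**Working it through.** The main check is a comparison of texts. Four kinds of child without a danger sign or stridor on the hospital examination were put through the rules:

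| Child at hospital | Rule in Intervention delivery | Referral-facility rule, Methods definition | Referral-facility rule, Abstract definition |
|---|---|---|---|
| Below 92% at home (confirmed) and at hospital, with fast breathing or in-drawing | Admit | Outpatient | Admit and outpatient clauses both met |
| Below 92% at home (confirmed) and at hospital, no fast breathing or in-drawing | Admit | Outpatient | Outpatient |
| Below 92% at home (confirmed), recovered at hospital | Admit | Outpatient | Outpatient |
| Control child first found below 92% at hospital | No rule applies | Outpatient | Outpatient (the wider definition covers the intervention arm only) |

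- **Row 1.** The Methods definition leaves SpO2 out, so the conflict is direct. The Abstract definition brings SpO2 into the admission clause indirectly, but the outpatient clause equates not severe with having no danger sign, so the same child satisfies both.
- **Row 2.** Hypoxaemia alone meets neither definition. Only the outpatient clause remains, against admission in Intervention delivery.
- **Row 3.** Here the two sections can be reconciled: the home reading prompts referral and the hospital examination supersedes it.
- **Row 4.** This is a gap rather than a conflict. The only rule that applies does not mention SpO2.

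**How many children.** The article gives no count, so this is an order of magnitude.

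- Total 4,160 (Sample size); equal arms assumed from the 1:1 cluster allocation: 4,160 / 2 = 2,080 per arm.
- Planned intervention acceptance 15% (Sample size): 0.15 × 2,080 = 312 reaching hospital. This treats acceptance as arrival, as the Strengths and limitations box does (verbal acceptance with a hospital visit).
- Share still below 92% without a danger sign: not in the documents, so a range is assumed.

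| Assumed share | Children | Share of the arm |
|---|---|---|
| 5% | 0.05 × 312 = 15.6 | 15.6 / 2,080 = 0.75% |
| 10% | 0.10 × 312 = 31.2 | 31.2 / 2,080 = 1.5% |
| 20% | 0.20 × 312 = 62.4 | 62.4 / 2,080 = 3.0% |

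**The case against.** The best defence is that the sections do different jobs. Intervention delivery acts on the health worker's reading at home. The referral-facility section is general triage for both arms after a fresh examination, and its outpatient branch is meant for children who turn out not to be severely ill. The physician will have just measured SpO2, staff are trained in IMNCI management of severe pneumonia, outpatient care follows the facility's own standard, and nothing forbids oxygen. An article also condenses hospital care that manuals may spell out.

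This reading works for a child whose saturation has recovered. It does not work for one still below 92%, because the outpatient clause is not conditional on the repeat reading. The reference to the facility's standard describes care once the outpatient route has been chosen; it does not govern the choice. A trained physician may well admit such a child, which makes harm less likely, but the article does not say so, and its section on compliance and deviations asks for strict adherence. Nor is this a detail left to a manual: both rules are printed in the article.

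Some of the objection stands:

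- The direct conflict is confined to intervention clusters.
- The counts are soft. The 4,160 are children with severe pneumonia, so children with hypoxaemia alone may lie outside that base. The Participant section also foresees accepters who never arrive, so 312 may be too high.
- Enrolment was far below plan. With the 235 reported for October 2020 (Study status; listed as cases and taken here as the intervention arm), 0.15 × 235 = 35.25 would reach hospital, and 5% to 20% of those is about 2 to 7 children.
- The Introduction defines hypoxaemia as below 90%, so whether a child at 90% or 91% needs admission is partly a clinical judgement. The trial's operative threshold, however, is 92%, and its own rule already requires admission below it.

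**Conclusion.** The concern holds. For a child hypoxaemic at home and again at hospital, with no danger sign, the article prescribes both admission for oxygen and outpatient care, and neither of its definitions of severe pneumonia removes the conflict. It is sharpest for hypoxaemia alone, where the referral-facility section leaves only outpatient care.

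The group is small: roughly 16 to 62 children at the planned size, resting on equal arms, 15% acceptance, acceptance meaning arrival, and an assumed 5% to 20% share. The contradiction itself does not depend on these figures. For each such child the difference could be serious. Duration of oxygen therapy, length of stay and treatment failure are exposed among children who reach hospital, in a direction and by an amount that the article does not allow one to state. The primary comparison is unaffected. The text should be changed.

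**What to change.** Reword the disposition rule in Procedure at referral facility along these lines:

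> Admit if signs of severe pneumonia are present or if SpO2 is below 92% on the study physician's reading. Treat as an outpatient only if there is no danger sign and SpO2 is not below 92%.

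As worded, this covers both arms, so it also closes the gap for control children. Add to Intervention delivery that children with hypoxaemia alone follow the same rule, with evaluation for cyanotic congenital heart disease in addition. Use the trial threshold of 92% throughout, not the 90% of the Introduction.

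The cost is a one-clause clarification, a short note to study physicians and facility staff, and possibly a few more admissions at hospitals to which the study does not supply oxygen. Sample size, randomisation and the primary analysis are unchanged. Recruitment was still under way when the article was written, so the change could protect children enrolled later.

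### An intervention-cluster child still below 92% SpO2 at hospital but with no danger sign is to be admitted under one rule and treated as an outpatient under another

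*Protocol article*

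**What the plan says.** **In the community.** The Intervention delivery section has the Lady Health Worker (LHW) look first for "signs and symptoms of severe pneumonia (fast breathing/chest in-drawing and one or more danger sign" (stridor is also listed), "and second, hypoxaemia (SpO2 <92%) using a handheld pulse oximeter". After a low reading, the nose is cleared with saline and the measurement repeated. Then: "If repeat reading shows hypoxaemia, the child will be referred to nearest designated referral hospital and admitted for oxygen via nasal or nasopharyngeal route", together with intravenous antibiotics. No danger sign is required.

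**Who is referred.** The Participant section states for intervention clusters: "Presence of severe pneumonia with or without hypoxaemia, or hypoxaemia alone will merit hospital referral (non-facilitated". Intervention delivery adds that children with hypoxaemia but no signs of severe pneumonia are sent so that cyanotic congenital heart disease can be excluded. That sentence does not say whether they are to be admitted.

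**At the hospital.** Procedure at referral facility expects both kinds of child: "Children with severe pneumonia and/or hypoxaemia as per LHWs who reach referral hospital premises will be examined and subjected to pulse oximetry again". The disposition rule that follows has two branches. The first is "If signs and symptoms of severe pneumonia are present, the child will be admitted for further appropriate treatment". The second is "if the symptoms are not severe (absence of danger sign), the child will be treated in outpatient care", following the facility's own standard. Neither branch mentions the oximetry result.

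**The concern.** Both rules are printed, and they disagree about the same child. Someone following the facility rule literally would send a child with a confirmed low saturation to outpatient care, while the intervention text says that child is admitted for oxygen.

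The protocol's own premises make this a safety matter. The Introduction reports a 4.3-fold higher mortality risk when pneumonia is accompanied by hypoxaemia, and says that clinical signs vary in how well they predict it. A disposition rule based only on clinical signs brings back the weakness that oximetry is meant to remove, and does so for the children whom only oximetry brings to referral. The 12-hourly monitoring is specified only for admitted children.

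Two secondary outcomes in Study aims and design, duration of oxygen therapy and duration of hospital stay, would also depend on which rule the physician at hand follows.

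**Working it through.** No arithmetic applies. The check is to take each type of LHW-referred child in an intervention cluster and read off what each section prescribes.

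| Child on the physician's assessment | Intervention delivery | Procedure at referral facility | Conflict? |
|---|---|---|---|
| (a) Fast breathing or in-drawing, danger sign, SpO2 below 92% | Admit | Admit | No |
| (b) Fast breathing or in-drawing, no danger sign or stridor, SpO2 below 92% | Admit | Outpatient, by the bracketed gloss on what is not severe | Yes, unless the abstract's definition is imported |
| (c) Hypoxaemia alone, SpO2 still below 92% | Admit | Outpatient | Yes |
| (d) No danger sign, SpO2 recovered to 92% or more | Admission was expected at referral | Outpatient | Not pressed: reassessment may properly change the plan |

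**Row (b).** The abstract's intervention-arm definition lets hypoxaemia take the place of a danger sign once fast breathing or in-drawing is present. If the facility rule used that definition, this child would have severe pneumonia and be admitted. Two things in the Methods point the other way. Intervention delivery describes the signs and symptoms clinically and lists hypoxaemia as a separate second assessment. The facility section itself equates not severe with having no danger sign. So row (b) is a conflict on the nearest wording, but one with a possible reconciliation.

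**Row (c).** The abstract's definition does not help, because it still needs fast breathing or in-drawing. The heart-disease sentence gives a reason for referral, not a disposition. The admission sentence after the repeat reading makes no exception for this group. The facility section expressly expects children referred for hypoxaemia, then has no branch that uses their reading.

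**Arms.** Control LHWs do not measure SpO2, and the admission sentence belongs to the intervention procedure. The direct contradiction therefore arises only for LHW-detected hypoxaemia in intervention clusters. In the control arm the facility rule is silent on SpO2, but no second rule contradicts it.

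**The case against.** The strongest reply has four parts.

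1. *The sections describe different stages.* The community text states what is expected at referral, and the physician's later assessment may override it. This holds for a child whose saturation has recovered. It does not explain why a child still below 92% on the physician's own reading should not be admitted.

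2. *Hypoxaemia alone has its own pathway.* Intervention delivery sends these children for cardiac exclusion, and Limitations speaks of cardiac evaluation resources for them; oxygen with intravenous antibiotics reads more naturally as pneumonia care. This stands in part. Routine antibiotics for this group need not be intended, and the fix should respect that. But no outpatient rule is given for them, and Limitations concedes that cardiac evaluation may not be readily available.

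3. *The abstract's definition already covers fast breathing or in-drawing with hypoxaemia.* This softens that case, as shown above, and leaves hypoxaemia alone untouched.

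4. *An article condenses.* The facility's standard, the staff training in the integrated childhood illness guidelines and the hospital forms may tell physicians how to act on SpO2. They may, and mere silence about the reading would be no finding. The point rests instead on two printed rules that disagree.

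**Conclusion.** The contradiction is real and minor. It concerns children in intervention clusters who remain below 92% on the physician's reading and have no danger sign. It is firm for hypoxaemia alone and weaker for fast breathing or in-drawing with hypoxaemia. It bears on safety and on oxygen duration and hospital stay. Enrolment, sample size and the primary outcome are unaffected.

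The size cannot be given, because the article does not state what share of attenders would be hypoxaemic without a danger sign. Three stronger readings are tempting, and the article does not support them:

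- **A ceiling from the design rates.** With equal arms, 4160 / 2 = 2080 per arm; 2080 × 0.10 = 208 control and 2080 × 0.15 = 312 intervention attenders, 520 in all. This is not a valid bound on the children affected. It includes 208 control children, to whom the conflicting admission rule does not apply. It also rests on a count of severe pneumonia cases that may leave out hypoxaemia alone.
- **A contradiction in both arms.** Only the intervention text supplies the opposing rule.
- **Misclassified referral acceptance.** The strengths and limitations list defines acceptance as verbal agreement with a hospital visit. A child who attends and is treated as an outpatient is correctly counted as having accepted.

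**What to change.** Amend the disposition rule in Procedure at referral facility:

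- SpO2 below 92% on the study physician's repeat oximetry is itself a criterion for admission and oxygen, with or without a danger sign.
- Outpatient care is limited to children with no danger sign and SpO2 of 92% or more.
- A child with hypoxaemia alone is admitted for oxygen and cardiac assessment, with antibiotics at the physician's judgement.

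Apply the same rule to control-arm attenders wherever the planned repeat oximetry is done. In that arm it is a consistent safety rule, not the repair of a contradiction. The qualification matters because Intervention delivery mentions handheld oximeters only for physicians at the centre serving the intervention clusters.

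The cost is a short text change and a note to the study physicians. The repeat reading is already planned, and admission of these children is already foreseen in the intervention text. The downside is a few more admissions.
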